# Institutionalizing postpartum intrauterine device (IUD) services in Sri Lanka, Tanzania, and Nepal: study protocol for a cluster-randomized stepped-wedge trial

**DOI:** 10.1186/s12884-016-1160-0

**Published:** 2016-11-21

**Keywords:** Postpartum contraception, IUD, Impact evaluation

## Abstract

**Background:**

During the year following the birth of a child, 40% of women are estimated to have an unmet need for contraception. The copper IUD provides safe, effective, convenient, and long-term contraceptive protection that does not interfere with breastfeeding during the postpartum period. Postpartum IUD (PPIUD) insertion should be performed by a trained provider in the early postpartum period to reduce expulsion rates and complications, but these services are not widely available. The International Federation of Obstetricians and Gynecologists (FIGO) will implement an intervention that aims to institutionalize PPIUD training as a regular part of the OB/GYN training program and to integrate it as part of the standard practice at the time of delivery in intervention hospitals.

**Methods:**

This trial uses a cluster-randomized stepped wedge design to assess the causal effect of the FIGO intervention on the uptake and continued use of PPIUD and of the effect on subsequent pregnancy and birth. This trial also seeks to measure institutionalization of PPIUD services in study hospitals and diffusion of these services to other providers and health facilities. This study will also include a nested mixed-methods performance evaluation to describe intervention implementation.

**Discussion:**

This study will provide critical evidence on the causal effects of hospital-based PPIUD provision on contraceptive choices and reproductive health outcomes, as well as on the feasibility, acceptability and longer run institutional impacts in three low- and middle-income countries.

**Trial registration:**

Trial registered on March 11, 2016 with ClinicalTrials.gov, NCT02718222.

**Electronic supplementary material:**

The online version of this article (doi:10.1186/s12884-016-1160-0) contains supplementary material, which is available to authorized users.

## Background

Postpartum access to insertion of an intrauterine device (IUD) is critical for meeting women’s need for long-acting but reversible contraceptive protection. The IUD is safe, effective, long-acting, reversible, and convenient, especially when inserted in the immediate postpartum period [1]. The postpartum IUD (PPIUD) does not interfere with breastfeeding, is safe for use by all women, including HIV-positive women, is associated with less discomfort and fewer side effects than interval IUD insertion, and allows women to obtain safe, long-acting (up to 12 years), highly effective yet reversible contraceptive protection that can be made readily available to women delivering in health facilities. In countries where women do not return for postnatal follow-up visits because of cost, distance, or health system challenges PPIUD offers a convenient and cost-effective postpartum contraceptive option.

Despite these well-established benefits of PPIUD, its uptake continues to be low. During the year following the birth of a child, 40% of women are estimated to have an unmet need for contraception [2]. Fewer than 50% of women in 30 of the 43 countries with recent Demographic and Health Surveys (DHS) used any method of contraception during 9-11 months postpartum, and in 12 of these countries the use was below 20% [3]. The copper-bearing intrauterine device (copper IUD) is a safe and effective method that can be used immediately after delivery [4]; yet, only in three of the 43 counties (Egypt, Kyrgyz Republic and Tajikistan), were 20% or more of postpartum users of contraception relying on this method [3].

A number of studies and systematic reviews have evaluated the safety, efficacy and acceptability of immediate postpartum insertion of IUDs (within 10 min of delivery of the placenta) compared to delayed postpartum insertion (more than 10 min to 48 or 72 h following delivery) or interval insertion (after four or six weeks following delivery). Two systematic reviews of the evidence confirmed the safety and effectiveness of postpartum IUD insertions [1, 5]. Fifteen studies included in the first review showed that immediate IUD insertion was safe when compared with delayed postpartum and interval insertion. Immediate postpartum insertion had lower expulsion rates when compared to delayed postpartum insertion, but had higher expulsion rates when compared to interval insertion. The authors also noted that immediate insertion following Caesarean delivery demonstrated lower expulsion rates than immediate insertion following vaginal delivery. The review by Grimes et al. (2010) covered nine randomized controlled trials and showed higher expulsion rates of immediate postpartum IUD insertion than interval insertion [5]. Eroğlu et al. (2006) is the only study to compare immediate postpartum insertion and delayed postpartum IUD insertions with interval insertion [6]. Among 268 women using TCu 380A IUDs in one hospital in Ankara, Turkey, expulsions within a year after insertion were the highest in the group that had delayed IUD insertion (70%) as compared to immediate postpartum insertion (37%) and to those receiving interval insertion (7%; *p* < 0.003) [6].

Several studies reported acceptability of postpartum IUDs in diverse settings when information and counselling on postpartum contraceptive methods was provided to women [7–9]. To expand the use of PPIUD, high-quality counselling during the antenatal period and training of physicians and midwives is critical [10]. However, in countries where antenatal care rates are low or antenatal care does not include counseling on postpartum contraception due to lack of provider time or training, women may not receive information on PPIUD before coming to the hospital for delivery. Despite higher expulsion rates, providers may counsel these women after delivery and offer PPIUD insertion after the 10-min window for immediate PPIUD insertion has passed. Expulsions will be lower if: (a) the IUD is inserted within 10 min after delivery of the placenta; (b) placement is sufficiently high in the uterine fundus; and (c) insertion is done by a specially trained provider [1, 11, 12].

This trial is an impact evaluation of an intervention implemented by the International Federation of Gynaecology and Obstetrics (FIGO) that seeks to institutionalize PPIUD services, both immediate and delayed insertion, as a routine part of antenatal counselling and delivery room services in Sri Lanka, Nepal and Tanzania.

## Methods

### Aims

This trial aims to determine the causal effect of the intervention on the uptake and subsequent continued use of PPIUD. The extent to which the intervention leads to the institutionalization of PPIUD services in the hospitals during and after the FIGO intervention, and to what extent the services diffuse to other hospitals or providers will also be assessed. In addition, the coverage and quality of postpartum contraceptive counselling and service provision will be measured, including women and providers’ satisfaction with these services.

Specifically, the study aims to determine:The coverage and quality of counselling for postpartum family planningThe causal effect of the intervention on effective access to postpartum IUD during and 12 months after the end of the intervention periodThe causal effect of the intervention on utilization of postpartum IUD during and 12 months after the end of the intervention periodThe causal effect of the intervention on postpartum contraceptive use and method mixThe quality of the IUD services provided during the intervention period measured by expulsions, complications, and discontinuationThe causal effect of the intervention on postpartum reproductive behaviour and outcomes, including pregnancy, fertility, and abortionThe satisfaction of providers with the training they received, provision of services and their perspectives on scaling up PPIUD servicesThe satisfaction of women with postpartum IUD services and reasons for non-use and discontinuationThe institutionalization and diffusion of the PPIUD interventionHealth system and cultural facilitators and barriers to the successful implementation, institutionalization, and diffusion of postpartum IUD services

### Ethics approval

Ethical approval as exempt was granted by the Harvard T.H. Chan School of Public Health Office of Human Research Administration as Harvard will only receive de-identified datasets, and each country received ethical approval from the appropriate national Institutional Review Board (IRB). More specifically, the study received approval from the Ethics Review Committee at the Faculty of Medicine at the University of Colombo in Sri Lanka, the Nepal Health Research Council, and the National Institute for Medical Research in Tanzania. Protocol amendments were submitted for review and approval to each country’s IRB whenever changes to the protocol, consent forms, or questionnaires were made.

### Randomization of hospitals

Because of the potential benefit of the intervention to all women, a cluster-randomized stepped wedge design was considered most appropriate for the study. Six hospitals were selected in each country to provide national geographic coverage, and were randomized into two groups of three. Facilities were matched by number of deliveries per year, and one was randomly selected from each pair to be assigned to Group 1 while the other was assigned to Group 2. Using Stata software, researchers at Harvard T.H. Chan School of Public Health generated a random number that was assigned to each hospital. The hospital with the higher random number in the pair was assigned to Group 2, while the hospital with the lower random number in the pair was assigned to Group 1. A full list of study facilities is available upon request. The study enrolment period for both groups will be 12 months in Tanzania and 18 months in Nepal and Sri Lanka. In Group 1, the baseline standard of care (SOC) period will be three months and the PPIUD intervention period will be nine months in Tanzania and fifteen months in Nepal and Sri Lanka. In Group 2, the baseline (SOC) period will be nine months and the PPIUD intervention period three months in Tanzania and nine months in Nepal and Sri Lanka. We can represent this design for each group as follows:

**Table Taba:** 

Time (months)	1-3	4-9	10-12 (Tanzania) 10-18 (Nepal and Sri Lanka)
Group 1 (Hospitals 1-3)	O	X	X
Group 2 (Hospitals 4-6)	O	O	X
where X = PPIUD intervention and O = control (standard of care provided)			

Due to the randomized nature, the causal effect of the intervention on the outcomes of interest can be estimated. In months 4-9, a randomized contrast can be made that will be controlled for any secular trends in outcomes. In addition, before-after contrasts will be made within hospitals controlled for all time-invariant differences in event rates between hospitals. The reference population for the study will be all women in the catchment area delivering in each hospital within a period of 12 months from the start of the study in Tanzania and within a period of 18 months in Nepal and Sri Lanka.

### Participant selection criteria

#### Women

Selection criteria for the study vary by country based on local regulations and the structure of the health system. In Sri Lanka, women will be eligible to participate in the study (inclusion criterion) if they deliver in one of the six study hospitals during the 18-month enrolment period, unless they normally reside outside of Sri Lanka. The study will interview women at up to four time points: baseline (in the hospital soon after delivery), 4-8 weeks postpartum for those who have PPIUD inserted, 9 months postpartum, and 18 months postpartum. In Sri Lanka, primary care services such as child immunizations are not available in the study hospitals, and the 9-month and 18-month surveys will be completed in satellite clinics affiliated with the study hospitals. There can be many satellite clinics affiliated with each hospital, and three to four will be selected based on geographic representation and the percentage of women delivering in the study hospitals who may receive postnatal care at the selected satellite clinics. Women enrolled at baseline will be eligible to complete the 9-month and 18-month surveys if they live in the catchment for one of the selected satellite clinics.

In Nepal, women will be eligible to participate in the study if they deliver in one of the six study hospitals during the 18-month enrolment period, unless they normally reside outside of the country. As in Sri Lanka, the study will interview women at up to four time points: baseline (in the hospital soon after delivery), 4-8 weeks postpartum for those who have PPIUD inserted, 9 months postpartum, and 18 months postpartum. In Nepal, because of the mountainous terrain and long travel times to reach remote areas, only women who live within 24 h of the study hospital will be eligible for the 9-month and 18-month follow up. Due to the high delivery caseload in the six hospitals selected in Nepal, a 55% sample of women enrolled at baseline who live within 24 h of the study hospital will be randomly selected to complete the two long-term follow up interviews at 9 months and 18 months postpartum. The long-term follow-up interviews will be conducted in the hospital when possible, but for participants unable to return to the hospital, enumerators will conduct interviews at the participant’s home or another location of the participant’s choosing.

In Tanzania, women will be eligible to participate in the study if they are age 18 or older and deliver in one of the study hospitals during the 12-month enrolment period, unless they normally reside outside of Tanzania. As in Sri Lanka, primary care services in Tanzania are not available in the study hospitals, and the 9-month and 18-month surveys will be completed in satellite clinics affiliated with the study hospitals. Three to four clinics will be selected based on geographic representation and the percentage of women delivering in the study hospitals who may receive postnatal care at the selected satellite clinics. In Tanzania, selection for the follow-up surveys is not dependent on enrolment at baseline. Data collectors will be posted at the selected satellite clinics, and women may be enrolled in the study at the time of the 9-month or 18-month survey when they visit the satellite clinics for child immunization services if they meet the eligibility criteria for the study (delivered in one of the six intervention hospitals during the 12-month enrolment period, normally reside in Tanzania, and are age 18 or older).

#### Providers

The provider sample includes all medical personnel who could potentially provide PPIUD who are working in the study hospitals during the 15-month intervention period, along with those who are working in the hospitals 12 months after the end of the study period. In Sri Lanka, only doctors are eligible to provide PPIUD services, and all eligible doctors were included. In Nepal and Tanzania, a random sample of providers was selected to participate in the Provider Survey. A full list of doctors and nurses eligible to provide PPIUD services was obtained, and stratified random sampling was used to select an equal number of providers from each cadre in each facility to complete the survey.

### The intervention

The International Federation of Gynaecology and Obstetrics (FIGO) has designed and will implement, through its nationally-affiliated Associations of Gynaecologists and Obstetricians, an intervention program on PPIUD services. As part of this Program, FIGO is responsible for the development and production of informational materials, training providers in counselling and in the provision of PPIUDs, improving facilities, ensuring good quality of service, and monitoring the program. Each component of the intervention is described in detail below.

#### Coordination with ministries of health

In order to introduce the provision of PPIUD services in a manner that is sustainable and achieves integration as part of the standard training and delivery practice, FIGO and their national affiliates will work closely with each country’s Ministry of Health to ensure adherence to national guidelines and to ensure quality of training and monitoring activities.

#### Training of providers

The facilities chosen in each country are primarily teaching hospitals who wish to include PPIUD as part of the regular OB/GYN training program and to integrate it as part of the standard delivery practice in these institutions. Health professionals will be trained through a combination of specific classroom-based training sessions and on the job training and mentoring, with new staff undertaking training as they rotate to the facilities.

Courses for approximately 12 master trainers, two from each participating hospital, will be organized. The training will include lectures, videos, web-based learning material, master classes and practical exercises on mannequins. Supervised IUD insertions and counselling sessions on patients will subsequently take place in order to establish competency.

These master trainers, who will be respected health care professionals with experience in implementing evidence-based clinical practices, will subsequently train the resident obstetrician/gynaecologists, the health facilities’ delivery team, the facilities’ antenatal team, and the community midwives in PPIUD related service delivery. All health providers involved in the project will be trained on counselling women on the benefits of adopting a postpartum contraceptive method for birth-spacing and maternal and infant health.

#### Training of community intermediaries

Community-based intermediaries, including midwives, skilled birth attendants and community health workers, are often the first point of contact for pregnant women in semi-urban areas. In an effort to increase the acceptance of PPIUD services, this intervention will orient community intermediaries linked with each hospital on postpartum contraception and PPIUD to enable them to integrate postpartum family planning content into their regular community-level activities, including counselling of pregnant women.

#### PPIUD service delivery

Women presenting at selected hospitals and associated clinics will receive information on postpartum contraception and the availability of PPIUD services during antenatal care and after delivery. The intervention will support printing of local government-approved leaflets on postpartum contraception and PPIUD to be used during counselling. In addition, the intervention will supply at least one TV for each hospital, and a video on postpartum contraception and PPIUD will be played in the local language. Informed consent for PPIUD will be obtained at the time of counselling and case notes marked for easy identification. Consent for PPIUD will be taken again immediately prior to PPIUD insertion and noted in the maternity records. Those women who have an IUD fitted will be encouraged to attend a follow-up visit with her midwife or the hospital/associated satellite clinic. Where possible, follow-up will be combined with the child’s 4-8-week immunization visit.

Each selected facility has a facility coordinator who will be responsible for working with the National Project Coordinator to have an effective stock management system in place and for ensuring that there are sufficient supplies of IUDs, proper inserters such as long curved Kelly’s forceps, clinical notes, patient information literature and consent forms.

#### Monitoring and mentoring

In order to track progress against the intervention’s objectives and to improve provider performance, FIGO and the in-country FIGO affiliates will regularly monitor service delivery data to provide support, if needed, to improve the performance of providers at the participating hospitals.

### Outcome measures

Study outcomes will be assessed using a variety of research instruments. Quantitative interviewer-administered surveys will be conducted with women at up to four time points:Baseline (in hospital after delivery)4–8 weeks after delivery among women who accepted PPIUDProviders ask women to get a PPIUD check-up at 4-6 weeks postpartum, and these data can be collected between 2-12 weeks after delivery
9 months after deliveryCan be collected 8-14 months after delivery
18 months after deliveryCan be collected 15-21 months after delivery

Quantitative interviewer-administered surveys will also be conducted with providers at three time points:Baseline, prior to implementation of FIGO intervention6 months after implementation begins12 months after implementation ends

A facility survey using a checklist will also be completed before the intervention, 6 months after the intervention has begun, and 12 months after the end of intervention implementation to examine the extent to which PPIUD counselling and services have been institutionalized.

Primary and secondary outcomes are listed in Additional file 1, and key outcomes of interest are described in greater detail below:Uptake of PPIUDTo ascertain what percentage of women delivering in study hospitals take up PPIUD, participants will be interviewed after delivery, before they are discharged from the hospital
Receipt of PPIUD counseling before or after deliveryTo ascertain what percentage of women delivering in study hospitals receive counseling on PPIUD, participants will be interviewed after delivery, before they are discharged from the hospital. They will also be asked questions to assess the quality of the counseling.
PPIUD expulsion rate and complication rate at 4-8 weeks postpartumParticipants who have not deliberately removed the PPIUD will be examined by providers at 4-8 weeks postpartum, and providers will report whether the PPIUD was expelled or complications occurred.
Modern contraceptive use at 9 months postpartumParticipants will be interviewed at 9 months and asked whether they are using a modern method of contraception, defined as pill, implant, injectable, IUD, condom, or sterilization for the purposes of this study.
Modern contraceptive use at 18 months postpartumParticipants will be interviewed at 18 months and asked whether they are using a modern method of contraception.
Pregnancy rate at 18 months postpartumParticipants will be interviewed at 18 months and asked whether they are currently pregnant or have had a pregnancy that was terminated.
Sustainability: Percentage of trained providers who are still providing PPIUD services 12 months after the end of implementationProviders originally trained under the FIGO intervention will be interviewed at 12 months after intervention implementation ends to assess whether PPIUD services have continued after intervention support ends, suggesting institutionalization of services in the facility.
Sustainability: Percentage of trained providers providing PPIUD services in new facilities (after transfer) 12 months after the end of implementationIt is expected that some providers originally trained under the FIGO intervention will be transferred to new facilities as is the practice in all three study countries. Providers originally trained under the FIGO intervention and transferred to new facilities will be interviewed 12 months after implementation ends to ascertain whether they continue providing services in their new facilities, diffusing PPIUD services to other parts of the country.
Sustainability: Percentage of new providers providing PPIUD services in intervention facilities 12 months after the end of implementation

New providers not originally trained under the PPIUD intervention, but who are working in intervention facilities will be interviewed 12 months after the end of intervention implementation to assess the diffusion of PPIUD services to other providers within the facility.

The study timeline and associated quantitative data collection activities for each of the two groups of hospitals are depicted in Fig. 1 for Tanzania and Fig. 2 for Nepal and Sri Lanka.

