### Sample size

Following the cluster-randomized stepped-wedge design, power calculations were performed on a per country basis, assuming that 300 women are enrolled per hospital per month over a 12-month study enrolment period in Tanzania and an 18-month study enrolment period in Nepal and Sri Lanka, and followed for up to 18 months postpartum to ascertain study endpoints [13]. It is expected that the study will enrol 21,600 women in Tanzania and 32,400 women in Nepal and Sri Lanka.PPIUD Counselling – Assuming that at the study hospitals during the standard of care time periods, the PPIUD counselling rate will be 1% or lower, we will have 80% power or more to detect an increased counselling rate of 2% or greater, even with an ICC of 15% [14] or lower, assuming that at least 21,600 women are enrolled during the 12-18-month enrolment period.PPIUD Uptake – Assuming that at the study hospitals during the standard of care time periods, the PPIUD uptake rate will be 1% or lower, we will have 80% power or more to detect an increased PPIUD uptake rate of 8% or higher, even with an ICC of 15% or lower.PPIUD Expulsion Rate at 6 weeks – Assuming that the PPIUD uptake rate increased to 8% during the intervention periods at the study hospitals, there will be 80% power or greater if the PPIUD expulsion rate is assumed to be 20% before the intervention [15] and drops to 5% or less after the intervention, for an ICC of 5% or less, even with 20% loss to follow-up postpartum or less. These analyses apply only to the intervention periods at the six hospitals, and are based upon a one-sample test for clustered data.Modern contraceptive use at 6 weeks and 18 months – Assuming that modern contraceptive use at 6 weeks will be 55% in Sri Lanka [16] and that it will increase to 62% due to the availability of PPIUD during the intervention periods, there will be 80% power or more to detect this difference or anything greater, even if 20% of the participants enrolled during the antenatal period are lost to follow-up by the six week postpartum milestone and if the ICC is 15% or less. In Tanzania and Nepal, power is greater due to significantly lower modern contraceptive use at 6 weeks in the control group. Scenarios are similar for modern contraceptive use at 18 months.Proportion pregnant within 18 months of index pregnancy – Assuming that 24% of women who enrol during the control periods are pregnant again within 18 months [17], there will be 80% power or more to detect a decreased proportion pregnant by 18 months of 19.4% or less, even if 20% of the clients enrolled during the antenatal period are lost to follow-up by 18 months and if the ICC is 15% or less.

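### As worded, the 18-month pregnancy outcome leaves out a repeat pregnancy that ended in a live birth before the interview, so it does not match the cumulative proportion used for power

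*Protocol article*

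**What the plan says.** Under Outcome measures, the protocol article describes the 18-month pregnancy outcome by what women are asked at interview: they are "asked whether they are currently pregnant or have had a pregnancy that was terminated". No third category is given for a repeat pregnancy that ended in a live birth. The same section allows the 18-month survey to be collected from 15 to 21 months after delivery.

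The Sample size section names the endpoint "Proportion pregnant within 18 months of index pregnancy". It assumes that "24% of women who enrol during the control periods are pregnant again within 18 months" and sets the detectable alternative at a "decreased proportion pregnant by 18 months of 19.4% or less". The claim is 80% power or more, allowing for 20% loss to follow-up, "if the ICC is 15% or less".

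The abstract sets out to estimate the intervention's effect on uptake and continued use and "of the effect on subsequent pregnancy and birth". The Aims section lists pregnancy, fertility and abortion among the reproductive outcomes.

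**The concern.** The power statement concerns a cumulative quantity: whether a woman has been pregnant again at any time up to 18 months. The interview wording captures something narrower: pregnant on the day, or a pregnancy that was terminated. The two differ by the women who conceived within roughly the first 6 to 12 months (interview month minus nine) and have since delivered. Those are the shortest birth intervals, which matter most to a trial with birth-spacing aims.

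If the wording is applied as written, three things follow:

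- The recorded control rate is not comparable with the planned 24%.
- The absolute effect, which Planned analyses says will be reported as a risk difference, is understated.
- The stated power belongs to an endpoint that is not the one measured.

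Because the interview can fall anywhere in a six-month window, the share missed also depends on the interview date.

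**Working it through.** **Inputs from the protocol article.** Control 24%, intervention 19.4%, ICC 0.15, 20% loss, 300 women per hospital per month, six hospitals in two groups of three, switches after months 3 and 9, interview at 15-21 months.

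**Assumptions of this check.** Two-sided alpha 0.05 (not stated in Sample size); a 9-month gestation; a constant conception hazard starting s = 0, 3 or 6 months postpartum, scaled to the plan's two percentages at month 18. Every pregnancy conceived more than nine months before interview is treated as a live birth. Early terminations would still be captured, so this slightly overstates the loss. Second repeat pregnancies are ignored.

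**Step 1. The plan's own figures.** Enrolment: 6 × 300 × 12 = 21,600 and 6 × 300 × 18 = 32,400, as stated. For power I used a stepped-wedge linear mixed model with fixed periods and a random hospital intercept.

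- Mean proportion (0.24 + 0.194)/2 = 0.217; total variance 0.217 × 0.783 = 0.1699.
- Between-hospital variance 0.15 × 0.1699 = 0.0255; within-hospital variance 0.85 × 0.1699 = 0.1444.
- Followed women per hospital: 240 a month, so 720, 1,440 and 720 in the three periods of the 12-month design.
- The generalised least squares standard error of the effect is 0.01155. Power = Φ(0.046/0.01155 − 1.96) = Φ(2.02) = 97.8%.
- For the 18-month design the standard error is 0.01001 and power is 99.6%.

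The claim of 80% or more therefore holds for the cumulative endpoint.

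**Step 2. Share missed at an 18-month interview.** Hazard h = −ln(1 − p)/(18 − s). Cumulative proportion by month x: F(x) = 1 − exp(−h(x − s)). Already delivered by interview month T: F(T − 9). Recorded: F(T) − F(T − 9).

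| Start s | Control F(9) | Missed, F(9)/0.24 | Recorded control | Recorded intervention | Difference | Risk ratio |
|---|---|---|---|---|---|---|
| 0 | 12.8% | 53% | 11.2% | 9.2% | 2.0 points | 0.82 |
| 3 | 10.4% | 43% | 13.6% | 11.1% | 2.5 points | 0.82 |
| 6 | 6.6% | 28% | 17.4% | 14.2% | 3.2 points | 0.82 |

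The planned contrast is 24 − 19.4 = 4.6 points, with a risk ratio of 19.4/24 = 0.81.

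**Step 3. Power with the recorded proportions.** Same model as Step 1, ICC 0.15.

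- 12-month design: standard errors 0.00847, 0.00923 and 0.01021; power about 66%, 76% and 88%.
- 18-month design: standard errors 0.00734, 0.00800 and 0.00885; power about 78%, 87% and 95%.

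**Step 4. The interview window.** For starts 0, 3 and 6, the missed share is 43%, 27% and 0% at 15 months, and 61%, 54% and 44% at 21 months.

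**Step 5. Sensitivity to the conception curve.** Conceptions uniform from month 2 to 18 give (9 − 2)/(18 − 2) = 44% missed at 18 months. A linearly rising hazard gives approximately (9/18)² = 25%. The 28-53% range is thus an illustration, not a bound.

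**Step 6. When the risk ratio moves.** In Step 2 the intervention lowers the hazard by the same factor throughout, and the ratio barely changes. Now suppose instead that the whole 4.6 points is prevented before month 9 (start 0). Recorded control is 24 − 12.8 = 11.2%, and recorded intervention is 19.4 − (12.8 − 4.6) = 11.2%. The effect disappears.

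**The case against.** The strongest reply is that the text describes an interview question, not a scoring rule. The surveys are in DHS format, their items are not shown, and Additional file 1, which lists the outcomes, is not shown either. Since birth and fertility are stated targets, births may well be collected. The 9-month interview might also catch some of these pregnancies while they are in progress.

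This stands as a limit on certainty: that such women would be scored as not pregnant is a consequence of the wording, not something the plan states. It does not remove the mismatch. Nothing shown feeds births into this outcome. The article ties the outcome to the 18-month interview, and in Tanzania women may first enter the study at that survey, so an earlier interview cannot be relied on. Reading a terminated pregnancy as one that ended in any way would close the gap, but the term does not ordinarily cover a live birth.

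A reader might also infer that the trial's effect estimate is biased towards no effect on every scale, because a device inserted at delivery prevents mainly early conceptions. The documents do not support that. The Background describes protection of up to 12 years, and under a constant relative effect the risk ratio goes only from 0.81 to 0.82.

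The 15-21 month window is a collection tolerance, and the documents give no reason to think it is used differently in the two conditions. Nor does the gap touch uptake, which Data collection procedures calls the primary outcome, although Sample size speaks of primary endpoints in the plural and includes pregnancy in that list.

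**Conclusion.** The point holds as a mismatch between the outcome as worded and the endpoint as powered. On the assumptions listed, about 28-53% of control pregnancies would be missed at an 18-month interview, and 0-61% across the permitted window. The recorded control rate would be about 11-17% instead of 24%, and the risk difference about 2.0-3.2 points instead of 4.6. Power in the 12-month design at ICC 0.15 would be about 66-88% instead of 98%, below the claimed 80% in two of the three scenarios. In the 18-month design it falls just below 80% in one.

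These sizes rest on assumed conception timing and on the plan's own enrolment and loss figures. The direction of the loss in the recorded rate does not depend on the particular curve, provided some women conceive early enough to deliver before interview. Attenuation of the risk ratio needs the further assumption that the effect is concentrated in early conceptions.

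**What to change.** Define the event as any pregnancy conceived after the index delivery and within 18 months of it, whatever its outcome: ongoing, live birth, stillbirth, miscarriage or induced abortion. Record the date so that a common 18-month cut-off can be applied, with women interviewed before 18 months treated as censored at interview. Use the same definition in Outcome measures and Sample size, including the same starting point, since Sample size counts from the index pregnancy. The choice of model can be left to the analysis plan.

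The cost is outcome wording and at most one or two dated questions in the 18-month survey, with no added participants. If the DHS-format questionnaire already collects dated births, a sentence saying that they count towards this outcome is enough.
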